### Patient recruitment and timeline

Patients are informed by their clinician about the ongoing research and are offered the opportunity to participate in the study. Upon expressing interest, parents will be approached by an independent researcher who will provide them with detailed information about the study. Interested parents will be asked to sign the consent form indicating their willingness to participate with their child (Consent Form, see online supplemental C). For all parents who decline participations or withdraw from the study, their reasoning for making this decision will be documented. In order to promote participant retention, parents will receive 10 euro gift cards for every complete set of questionnaires.

Enrolment of participants and their parents has started in September 2022. The study follow-up period will extend until either participants reach the age of 8 years or until the end of the inclusion period (September 2030), whichever comes first. Currently, there are 90 participants included in this study (September 2024).

### Data collection & management

Data will be handled confidentially and anonymously. After receiving the signed consent form from the parents, every participant receives a unique study number that is used to link the data to the child. The coordinating researcher safeguards the key to the code.

All data from the questionnaires will be collected with GemsTracker, a software package for the distribution of digital questionnaires. Parents of patients receive emails at appropriate times with a secured link to GemsTracker’s website to answer questionnaires digitally. Both the emails as well as reminders, if questionnaires remain incomplete, are sent automatically with a maximum of two reminders. All data from clinical follow-up will be collected from the medical records. The coordinating researcher will regularly monitor whether all data are registered timely and properly. The combined data from both GemsTracker and the medical records are collected in Castor, a secured database. Daily back-ups are made automatically. Storage of personal data will be in line with the Dutch General Data Protection Regulation. Data access control will be in the hands of the principal investigator. Research data will be preserved for 10 years, according to national law. In the case of discontinuation of a participant, only data collected up until that point will be included.

### Statistical methods

#### Primary outcome

The primary outcome measurement of the head circumference is transformed to an age-specific and sex-specific SD score, according to national norms. The yearly decline in head growth is chosen as the primary outcome since this continuous measure has more power, allowing us to adjust for possible confounders. This would not be possible when using binary outcomes with low prevalence (eg, presence/absence of papilledema at funduscopy). Non-inferiority with regard to head growth from 0 to 8 years (yearly difference in SD score) is determined using a linear mixed model adjusted for potential confounders (including severity of phenotype, sex, syndrome and parental factors) and comparing the lower bound of the 95% CI of the treatment effect estimate (conservative vs surgery) to the non-inferiority margin of −0.5 SD.

#### Secondary outcomes

The presence or absence of papilledema on funduscopy is analysed with a repeated measures logistic regression to compare difference between the two groups. Prevalence of orthoptic anomalies is compared between the two groups and compared with the norm data, using the χ^2^ test. If the number of cases allows for estimating parameters, a logistic regression model is used; otherwise, the outcomes are stratified by treatment arms. Pearson’s correlation coefficients are calculated to determine a correlation between the VAS and the 2D photo grading and the VAS and the 3D photo grading per time point. For all validated instruments, norm values are available, including cut-off levels. Comparison will be made for the outcomes of the instruments between the two treatment groups and with the norm data. For some of the above-mentioned variables, different instruments are used at various time points to measure a single construct. In this case, the (ordinal) scores obtained from the instruments will be compared between the two groups at each time point using an independent-sample t-test. In case of repeated measures of a construct using the same instrument, we will use mixed-model analysis to compare the change of the given outcome over time between the two groups. In the case of multiple analyses that target the same research question, multiple testing correction will be applied. We will control the type I error rate using Bonferroni correction. As far as possible, missing data will be imputed and the number of patients used for analysis at each stage of the study shall be reported.

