Over the course of the past 6 years at Erasmus Sophia Children’s Hospital (Rotterdam, The Netherlands), approximately two-thirds (142/216) of parents of patients with metopic synostosis chose conservative treatment, while the remaining one-third opted for surgical treatment. None of the conservatively treated patients developed signs of increased intracranial pressure nor required craniofacial surgery. The choice of conservative treatment extends beyond its clinical consequences, influencing financial expenses associated with the management of patients with craniosynostosis. Although studies in the field of craniosynostosis have compared costs and established the cost-effectiveness of various surgical techniques,^29^,^31^ an evident gap exists in the literature concerning cost-effectiveness analyses comparing conservative and surgical treatments, particularly in patients with metopic synostosis.

Taking into account the sporadic occurrence of increased intracranial pressure and the overall tendency to have worse cognitive, behavioural and ophthalmologic outcomes even after surgery, the functional indication for surgical intervention for patients with metopic synostosis seems uncertain. In the existing literature, all outcomes following conservative treatment for patients with metopic synostosis are hard to determine due to small sample sizes, relatively short duration of follow-up and mild characteristics in the majority of the conservatively treated patients.^1426^,^28 32^ Therefore, a prospective cohort study with adequate follow-up is needed to determine if a conservative policy is as effective as surgical intervention. We present the study protocol for an observational cohort study on the effectiveness of a conservative policy compared with craniofacial surgery in metopic synostosis. This study presents a unique opportunity to assess differences in outcomes between conservatively and surgically treated patients with metopic synostosis in domains including intracranial pressure, vision, cognitive and behavioural functioning, impact on family and child, aesthetic outcomes and societal costs.

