### Study design

Based on discussions with the patient society LAPOSA, an observational cohort design was chosen as the study design instead of a randomised trial, because randomisation of the type of treatment is not accepted by parents.

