### Interventions

The study protocol aligns with our current clinical protocol up until the age of 8 years, except for additional questionnaires. At our centre, as of 2017, treatment decisions are made through a shared decision-making process in which parents can choose between two treatment options: conservative treatment or surgical treatment. Conservative treatment involves a nonsurgical approach with yearly routine follow-up appointments. The choice of the type of surgical treatment depends on the age at presentation and parental preferences, with two options available: fronto-orbital advancement and endoscopic-strip craniectomy with helmet therapy. If parents opt for a conservative policy, surgery is only performed if raised intracranial pressure occurs.

All patients with metopic synostosis receive identical follow-up care, irrespective of whether they undergo surgical or conservative treatment. This entails yearly hospital visits until the age of 8 years, followed by subsequent visits every 3 years until the age of 18 when craniofacial growth is considered to have reached its final stage. Head growth is measured every visit and funduscopy is performed annually up to the age of 4 years. Assessment of refractive errors occurs at 1, 4 and 8 years of age. Psychological screening is routinely offered between the ages of 2 to 8 years. 2D and 3D imaging is performed every other year at the ages of 0, 2, 4, 6 and 8 years.

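### No confounder adjustment is specified for any secondary outcome, and the t-test and χ² test named for cognition and orthoptic anomalies cannot provide it in a cohort where parents choose the treatment

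*Protocol article*

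**What the plan says.** Under Study design, the protocol article states that "an observational cohort design was chosen as the study design instead of a randomised trial". Under Interventions, "treatment decisions are made through a shared decision-making process in which parents can choose between two treatment options". Syndromic and non-syndromic children are both eligible (Eligibility criteria).

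Under Statistical methods, Primary outcome, head growth is analysed with a "linear mixed model adjusted for potential confounders (including severity of phenotype, sex, syndrome and parental factors"). The same paragraph explains that a continuous outcome was preferred partly because it permits this adjustment, which it considers impossible for binary outcomes of low prevalence such as papilledema.

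Under Secondary outcomes, no confounder is named. The methods given are:

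- **Constructs measured with different instruments at different ages:** scores "will be compared between the two groups at each time point using an independent-sample t-test". By Table 1 this is chiefly development and cognition (ASQ-extended, BSID-III, WPPSI-IV, WISC-V).
- **Orthoptic anomalies:** "Prevalence of orthoptic anomalies is compared between the two groups and compared with the norm data, using the χ^2^ test". Logistic regression follows if there are enough cases; its covariates are not stated.
- **Constructs repeated with the same instrument** (by Table 1: SDQ, KJTS, PCL-5, OBVL, PedsQL, EQ-5D-Y): a mixed model for change over time.
- **Papilledema:** repeated measures logistic regression.

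**The concern.** The article accepts that the two groups may differ in ways that affect outcome, and acts on this for head growth. The same children, with the same treatment choice behind them, supply the secondary outcomes. Syndrome and parental factors are plausible determinants of developmental scores and IQ, and severity may influence both the choice of treatment and eye findings. A t-test or χ² test attributes the whole group difference to treatment.

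These comparisons carry weight. The Introduction describes the direct comparison of cognition and behaviour between the two policies as missing from the literature, and lists vision and cognition among the domains the study will compare. Ethics and dissemination says the results will enter practice and lead to an update of the Dutch guideline. The Bonferroni correction planned for multiple analyses controls chance findings, not confounding, and a larger cohort only makes a biased contrast more precise.

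**Working it through.** **1. The plan's own figures.** The article gives no power or precision figure for a secondary outcome. Its 90% power concerns the primary test and is not disputed here.

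**2. Does the article's reason for not adjusting apply?** The only reason it offers is low prevalence of a binary outcome. Cognitive scores are not binary. The Introduction reports hyperopia in 22% and astigmatism in 23% of patients. With 450 children, 0.22 × 450 = 99 and 0.23 × 450 = 103.5 expected cases if all are examined, which is enough to fit a logistic model with a modest covariate set. The reason does fit papilledema (1.8% in surgically treated non-syndromic patients, per the Introduction).

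**3. Bias of a crude cognitive contrast.** The article reports neither severity nor syndrome by arm, so every imbalance below is assumed.

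Bias = (difference in syndromic share) × (score deficit in syndromic children). With an assumed deficit of 15 points:

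- difference 0: 0 points
- difference 0.10: 0.10 × 15 = 1.5 points
- difference 0.20: 0.20 × 15 = 3.0 points

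A reversed imbalance gives the same values with the opposite sign.

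For comparison, the 95% half-width with SD 15 and the simulation's 245 and 195 children (Power & sample size considerations) is 1.96 × 15 × √(1/245 + 1/195) = ±2.8 points if every child is tested. Follow-up stops in September 2030, so fewer reach age 8. With 120 and 95 (about half) it is 1.96 × 15 × √(1/120 + 1/95) = ±4.0. The bias stays the same but is smaller relative to the interval.

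**4. False-positive rate of the t-test.** Assume no treatment effect, a binary severity factor with severe shares p_s (surgery) and p_c (conservative), and an effect of d residual SDs. Then bias b = d(p_s − p_c), SE = √[(1 + d²p_c(1−p_c))/n_c + (1 + d²p_s(1−p_s))/n_s], and the two-sided 5% test rejects with probability 1 − Φ(1.96 − b/SE) + Φ(−1.96 − b/SE).

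| p_s vs p_c | d | b (SD) | Rate, 245/195 | Rate, 120/95 |
|---|---|---|---|---|
| 50% vs 40% | 0.2 | 0.02 | 5.5% | 5.2% |
| 50% vs 30% | 0.3 | 0.06 | 9.5% | 7.2% |
| 60% vs 30% | 0.5 | 0.15 | 33% | 18.6% |

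In 4,000 simulated data sets per row at 245/195, the crude test rejected in 5.6%, 9.4% and 31.8%. A linear model including severity rejected in 4.8% to 5.1%.

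**5. χ² test.** Take 22% overall prevalence, no treatment effect, an assumed severity odds ratio of 1.5 to 3 and severe shares of 50–60% versus 30%. Expected prevalences then run from 22.8% versus 21.4% to 25.1% versus 19.5% (surgery versus conservative). The chance of a significant result in the direction of the imbalance runs from about 5.5% to 29%, against 2.5% in that tail without confounding.

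**The case against.** The strongest reply is that this is a condensed article: covariate lists for secondary models are often left to the analysis plan, and the mixed and logistic models could carry them. For those models that is fair, since silence there is not a wrong method. It does not cover the t-test and the χ² test, which are stated methods that exclude covariates. An adjusted analysis of cognition in a later plan would depart from the published one.

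Four stronger readings are tempting, and the article does not support them:

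- *All psychological outcomes get crude t-tests.* They do not. Behaviour, trauma, parenting stress and quality of life repeat the same questionnaire and go to mixed models.
- *Orthoptic outcomes are only ever compared crudely.* Logistic regression is foreseen if cases allow, and at 22% and 23% that branch is likely for the common refractive errors. Whether it would be adjusted is not said.
- *The conservative group is milder, so the bias favours conservative treatment.* The words "mild characteristics in the majority of the conservatively treated patients" describe earlier studies. Case mix by arm in this cohort is not reported, so the direction is unknown.
- *The economic evaluation has the same fault.* That section fixes no unadjusted test, so nothing there is stated wrongly.

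It is also fair that the bias figures rest on assumed inputs, and that the mildest scenario leaves the error rate almost nominal.

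**Conclusion.** The point holds for the two methods that are stated. Adjustment is specified only for the primary outcome, and the t-test for development and cognition and the χ² test for orthoptic anomalies cannot supply it. If followed as written, those contrasts confound treatment with case mix. For the mixed models and logistic regressions, the finding is only that no covariates are named.

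The size is unknown. It ranges from nothing, if the groups happen to be balanced, to a bias comparable with the whole 95% half-width (3.0 against ±2.8 IQ points) under the larger assumed imbalance. The case for adjusting needs neither a known size nor a known direction; it needs only parental choice of treatment and the article's own list of confounders. The primary non-inferiority analysis is not affected.

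**What to change.** Amend Secondary outcomes as follows:

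- **Cognition, at each time point:** replace the t-test with linear regression (ordinal regression for ordinal scores) on treatment plus the primary-analysis confounders.
- **Orthoptic anomalies:** make logistic regression with the same confounders the main between-group comparison where event numbers allow.
- **Repeated questionnaires:** include the same covariates in the mixed models.
- **Reporting:** give adjusted differences (odds ratios for binary outcomes) with 95% confidence intervals. Label the t-tests, χ² tests and rare-event comparisons as unadjusted and descriptive.

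The cost is wording and a little more analysis. The confounders are already needed for the primary model, so no new data are required. Children with missing covariates would drop out unless these are imputed, which fits the article's intention to impute where possible. With 90 children included by September 2024 and the inclusion period ending in September 2030, the change can be prespecified well before the final analysis.

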Each simulated data set contained 245 and 195 children in the conservative and surgery arm, respectively. The number of available observations at each measurement time decreased with increasing age, taking into account the sequential inclusion of children throughout the study period (and resulting differences in length of follow-up). The differences in SD scores between subsequent measurements were calculated and modelled using a random-intercept linear mixed model that had the treatment arm as the only fixed effect. The resulting parameter estimate for the treatment arm describes the difference in the yearly decline of SD score in the conservative arm compared with the surgery arm. Non-inferiority was defined as the lower bound of the 95% CI of the treatment effect estimate being larger than −0.5 SD.

Assuming an average yearly decline in head circumference SD score of −0.25 in the conservative arm resulted in 90% power to demonstrate non-inferiority of the conservative arm at a 2.5% one-sided significance, with a non-inferiority margin of −0.5 yearly SD difference.

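### Holm would give the same family-wise control as the Bonferroni correction fixed for related secondary analyses and never reject less: a cheap, low-priority improvement

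*Protocol article*

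**What the plan says.** The multiplicity rule is in the protocol article under Secondary outcomes. It has a scope and a method. The scope is: "In the case of multiple analyses that target the same research question, multiple testing correction will be applied". The method is: "We will control the type I error rate using Bonferroni correction".

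The same section shows where several tests of one question will arise. Where a construct is measured by different instruments at different ages, scores are "compared between the two groups at each time point using an independent-sample t-test". Where one instrument is repeated, "we will use mixed-model analysis to compare the change of the given outcome over time between the two groups", which may yield a single test and need no correction. Cognition is the clearest case of the first kind: Table 1 lists the BSID-III-NL at 2 years, the WPPSI-IV-NL at 4 and the WISC-V-NL at 8, hence at least three tests.

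The article does not list the families, the number of tests in each, or a significance level for secondary tests.

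**The concern.** The article does not leave the method open; it names one. Bonferroni compares every p-value in a family of m tests with 0.05/m. Holm compares the smallest with 0.05/m, the next with 0.05/(m−1), and so on, stopping at the first failure. Both control the family-wise error strongly whatever the dependence between tests, and any hypothesis that Bonferroni rejects is also rejected by Holm. As a testing procedure Bonferroni is therefore dominated.

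What is at stake is modest but not nil. The secondary comparisons of cognition are difference tests, with no non-inferiority margin. If the two policies truly differ at several ages, Bonferroni will declare fewer of those differences than the same error allowance permits.

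**Working it through.** **No figure of the plan to reproduce.** The article gives no adjusted level, family size or secondary power. Its stated power ("resulted in 90% power to demonstrate non-inferiority of the conservative arm at a 2.5% one-sided significance") belongs to the primary outcome and is not affected.

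**Inputs from the article.** Group sizes: "Each simulated data set contained 245 and 195 children in the conservative and surgery arm, respectively" (Power & sample size considerations).

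**Assumed, because the article does not give them.** Standardised difference d = 0.30 for each true effect; two-sided 5% per family; normal test statistics; equal group sizes at every time point; independence (correlation 0.5 as a check); family size m from 2 to 14.

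**Step 1: Bonferroni is valid.** For m independent true null hypotheses the family-wise error is 1 − (1 − 0.05/m)^m: 0.0494 (m = 2), 0.0491 (m = 4), 0.0489 (m = 14). With no correction it is 1 − 0.95^m: 0.0975, 0.1855 and 0.5123.

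**Step 2: Bonferroni power per test.** The standard error of d is √(1/245 + 1/195) = 0.0960, so the expected test statistic is 0.30/0.0960 = 3.126. Power is Φ(3.126 − z), with z the two-sided critical value at 0.05/m:

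- m = 2: z = 2.241, power 81.2%
- m = 3: z = 2.394, power 76.8%
- m = 4: z = 2.498, power 73.5%
- m = 8: z = 2.734, power 65.2%
- m = 14: z = 2.914, power 58.4%

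**Step 3: Holm by hand for m = 2.** Power at the unadjusted 5% level is Φ(3.126 − 1.960) = 87.8%. Under Holm a hypothesis is rejected if p ≤ 0.025, or if 0.025 < p ≤ 0.05 and the other p is at most 0.025.

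- Both effects real: 0.812 + (0.878 − 0.812) × 0.812 = 0.866, a gain of 5.4 points.
- One effect real: 0.812 + (0.878 − 0.812) × 0.025 = 0.8135, a gain of 0.17 points.

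The extra power is conditional on another rejection in the same family. That is why it nearly vanishes when only one effect is real.

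**Step 4: larger families by simulation** (200,000 families, independent tests). Entries are average power per true effect, Bonferroni → Holm.

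| m | One real | Half real | All real |
|---|---|---|---|
| 2 | 81.4% → 81.5% | as one real | 81.2% → 86.6% |
| 3 | 76.9% → 77.0% | – | 76.7% → 85.3% |
| 4 | 73.4% → 73.5% | 73.5% → 76.0% | 73.5% → 84.0% |
| 8 | 65.3% → 65.3% | 65.2% → 68.9% | 65.2% → 79.1% |
| 14 | 58.4% → 58.5% | 58.4% → 62.3% | 58.4% → 72.2% |

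At correlation 0.5 with all effects real, the gain is slightly smaller: m = 3, 76.8% → 83.7%; m = 4, 73.6% → 81.9%.

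**Step 5: what does not change.** Both methods use 0.05/m for the smallest p-value, so the chance of at least one rejection is identical (m = 4, all real: 99.5% under each). The simulated family-wise error stayed below 5% under both.

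**The case against.** The strongest reply is that this is a preference. Bonferroni is valid and prespecified, no stated figure changes, and nothing in the article contradicts it. That stands, and it limits the point to an optional efficiency gain.

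Several stronger readings are tempting and should be resisted:

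- *That the correction burdens every secondary outcome.* The stated scope is several analyses of one research question. A repeated instrument analysed by one mixed model may need no correction.
- *That missing a real disadvantage of a policy is the trial's main risk, and Holm guards against it.* The article does not say this. On the primary outcome, protection comes from "comparing the lower bound of the 95% CI of the treatment effect estimate (conservative vs surgery) to the non-inferiority margin of −0.5 SD", which the rule does not touch. For a single real difference in a family, Holm adds almost nothing.
- *That correlated outcomes make the case stronger.* Holm does not exploit correlation, and the gain is no larger at 0.5 than at 0.
- *That the largest gains are typical.* They need every hypothesis in the family to be false and equal numbers at each age. The article says that observations become fewer with age, and follow-up ends at age 8 or in September 2030. Under an assumed decline over three tests (200/120, 150/90 and 50/30 children, all effects 0.30), average power goes from about 39% to 44%, a gain of about 5 points.

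There is also a practical argument for Bonferroni. Its threshold is fixed in advance, so results at 2 and 4 years could be declared before those at 8 years exist. Holm needs the whole family first. The article does not say that ages will be reported separately, and for a final analysis this matters little.

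**Conclusion.** The point holds as a cheap, low-priority improvement and not as an error. Wherever several secondary analyses share a research question, Holm keeps the same family-wise guarantee and never rejects less. The benefit is negligible when one member of a family differs and material only when several do. The percentages depend on the assumed effect size, family sizes and constant group sizes; that Holm never rejects less does not. The primary non-inferiority analysis and its power are unaffected.

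**What to change.** In the Secondary outcomes section, replace the sentence that names Bonferroni with:

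> *Within each research question the family-wise type I error rate is controlled at 5% with the Holm procedure.*

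This is one sentence; it needs no extra data and alters no stated figure. It has two costs. Simple Bonferroni-widened simultaneous intervals would no longer agree with the test decisions. All p-values in a family must also be available before the decisions are final, so if results by age are to be declared as they mature, keeping Bonferroni for that family would be a reasonable choice.
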